## Abstract

Primary dysmenorrhea (PD) is a common gynecological disorder characterized by cramping pain in the lower abdomen during menstruation, in the absence of identifiable pathology. While Transcutaneous Electrical Nerve Stimulation (TENS) is used to promote PD pain relief, there is still a need to understand the parameters and cost-effectiveness of this intervention. As such, this study aims to disclose a study that will evaluate the effectiveness and cost-effectiveness of TENS on pain intensity in women with PD. This is a protocol for an assessor-blinded randomized controlled trial that includes 174 women with PD, >18 years old, with menstrual pain greater than or equal to four points in the Numerical Rating Scale. Participants will be randomized into three groups (active TENS, placebo TENS, and educational booklet). Participants allocated to the active TENS group will receive electrical stimulation (F = 100 Hz, pulse duration = 200 μs, for 30 min). In contrast, the placebo TENS group will receive placebo stimulation (same parameters, but for only 30 s, and then the current will be ramped off over a 15-s time frame) for three consecutive months during menstruation. Participants allocated to the educational booklet group will receive instructions about health promotion and education actions related to PD. A blinded assessor will evaluate the pain intensity (Numerical Rating Scale), presenteeism (Stanford Presenteeism Scale), Health-Related Quality of Life (Short-Form 6 dimensions and SF-36), and health costs of menstrual pain. This is the first study to propose a health economic evaluation while assessing the benefits of using TENS to treat PD symptoms. It is hypothesized that active TENS will be more effective than placebo TENS or the educational booklet in improving clinical outcomes in the short-, medium- and long-term. The study will also provide information about the cost-effectiveness of TENS, which can be used by policy makers to improve PD care in public and private health systems.

## Introduction

Primary dysmenorrhea (PD) is a common gynecological condition characterized by pelvic/abdominal pain before or during the menstrual period in the absence of pelvic disorder [1, 2]. It is believed that the prostaglandin release that occurs after the progesterone levels fall at the end of the luteal phase of the menstrual cycle is responsible for the uterine contractions and pain that characterize this disorder [3]. The prevalence of PD varies from 45% to 95% [4] in women of reproductive age [1]. In Mexico, a survey of 1,266 university students showed a prevalence of 66.9% in women aged between 21 and 23 years [5].

Common symptoms associated with PD are nausea, headache, tiredness, intestinal dysfunction, low back pain, irritability, and adynamia [2]. Often, PD and its symptoms lead to disability in performing daily life activities, being the leading cause of absence from school [6] and work [7] of adolescents and women, respectively. It was estimated that this phenomenon would cost approximately USD 2 billion of economic loss in the mid-1980s [8]. Among the most used interventions for PD are analgesics, nonsteroidal anti-inflammatory drugs, and hormonal contraceptives [9]. Nonetheless, they may present a failure rate of 20–25% and adverse effects such as indigestion, headaches, and drowsiness [10]. Consequently, nonpharmacological alternatives may be used to obtain symptom relief; the most common are regular physical activity [11], topical heat [12], acupuncture [13], and transcutaneous electrical nerve stimulation (TENS) [14–17].

TENS is widely used for any kind of pain [18, 19], and is a non-invasive technique that uses electrical stimulation applied through the skin to produce analgesia by peripheral nerve stimulation [20], among other physiological effects. TENS works by activating the δ-opioid and μ-opioid receptors in both the central and peripheral nervous systems [18, 19]. TENS can lead to increased blood flow to the targeted area by the axonal reflex [21], and, when used during a PD episode, TENS may decrease uterine ischemia as it may increase blood flow in the area of the dermatome corresponding to the uterus [16, 22]. TENS is recommended for women not willing to use conventional therapy for PD, with a recommendation level B [23]. TENS has been widely used for pain relief in PD [15–17, 24, 25], but the lack of information on the parameters used, randomization, and outcomes renders it difficult to replicate such studies [14, 16].

Economic analyses are essential in administrating and managing health services and improving healthcare quality based on scientific evidence [26]. Usually, public policies focused on a disease come from studies that identify the best evidence-based intervention with the lowest costs by analyzing the cost-effectiveness and cost-utility of that intervention. This allows governments to correctly direct finite resources to address the most critical issues in public health problems [27]. With the number of women affected by PD, this condition should be considered a public health problem that must be addressed by policymakers. Although it is known that women with PD are willing to spend more money on a cure for their symptoms compared to women without PD [28], and may spend two- to threefold more on medical consultations [29], the costs associated with PD treatment are still not clear [28], especially regarding nonpharmacological interventions such as TENS.

The general objectives of this research are to investigate if TENS can be effective in treating PD symptoms and to determine the cost-effectiveness associated with this intervention. The hypothesis of the study is that TENS will be effective and cost-effective for the treatment of PD symptoms. This article aims to describe the methods and statistical analysis of this study so that this information can be made public.

## Methods and analysis

### Study design and ethical aspects

This is a study protocol for a randomized controlled clinical trial with a health economic evaluation. The research was approved by the Ethics Research Committee of the Universidade Federal de São Carlos (UFSCar) (CAAE: 16530619.3.0000.5504, protocol number: 3.588.121). This study was registered at the Brazilian Registry of Clinical Trials (ReBEC) under the number RBR-5bxtgx (date of registration: November 1, 2019). Participants will be informed about all study procedures, and those who agree will be asked to sign the informed consent form prior to their enrollment in the study.

### Study setting and recruitment

This trial will be conducted in the Laboratory of Research in Women’s Health at UFSCar’s Physical Therapy Department. The study will be disclosed on social media, websites, and leaflets; prospective participants will be invited through an informal invitation and social media. All women who want to take part in the study will have their names, ages, and telephone numbers registered for posterior contact. After the first telephone contact, women will be screened for eligibility criteria, and eligible women will be invited to participate in the study. This study will be carried out following the Standard Protocol Items: Recommendations for Interventional Trials (SPIRIT) statement for clinical trial protocols [30].

### Sample size calculation

A recent systematic review showed that the effect size of TENS for PD was about 1.384 [31]. However, other studies that have used TENS as a primary intervention for PD did not look into the economic costs of the intervention or had other confounding factors analyzed as well. As such, the authors of the present study opted for a more conservative sample size calculation, with a much lower effect size. Therefore, the sample size calculation was performed with G*Power software (v.3.1.9.2, Dusseldorf, Germany), considering the comparison of three independent groups at five timepoints (baseline and months 1, 2, 3, 6 and 12 after baseline), with analysis of variance for repeated measures, a β value of 15%, an α of 5%, and an effect size (f) of 0.20, considering a dropout rate of 15%, resulting in 174 participants in the study (58 participants per group).

### Eligibility criteria

Participants’ inclusion criteria are as follows: women, nullipara, aged between 18 and 45 years, regular menstrual cycle, and presence of PD (pelvic or lower abdominal pain, occurring from 48 h before the onset of the menstrual period to 72 h after the first day of menstruation [2]) with pain intensity greater than or equal to four points in the Numerical Rating Scale (NRS) on the three menstrual cycles prior to their participation. The NRS considers 0 as no pain, 1–3 as mild pain, 4–7 as moderate pain, and 7–10 as severe pain [32], and only women with moderate to severe pain will be included, as more women rate their PD pain as moderate [33]. In addition, moderate to severe menstrual pain is associated with decreased quality of life [34]. Exclusion criteria for this study are as follows: pregnant, women using any kind of intrauterine device, women with skin lesions in the area where the electrodes will be placed, women with self-reported neurological or cardiac diseases, and women diagnosed with gynecological disorders (endometriosis, adenomyosis, uterine fibroids, etc.) that may be associated with secondary dysmenorrhea. The presence of any signs of skin irritation that may be associated with electrostimulation will be considered as a criterion to discontinue treatment. No concomitant care or interventions will be encouraged or forbidden during the study, but rather registered in the participant’s file.

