### Assessment of clinical outcomes

Participants who agree to participate will be assessed by a blinded assessor who will check for eligibility criteria. Subsequently, the blinded assessor will collect participants’ demographic and anthropometric data and information regarding menstrual pain medication use. Next, all eligible participants will be randomized and allocated into three groups: active TENS (aTENS), placebo TENS (pTENS), and minimum intervention group (booklet). The same blinded assessor will evaluate primary and secondary outcomes.

The primary outcome is pain intensity at baseline and three and six months after randomization. The secondary outcomes are pain intensity (only at 12 months after randomization, for the cost-utility analysis), health-related quality of life at 6 and 12 months after randomization, and pain intensity at each session before and after treatment for three months for the TENS groups. All assessment sessions are described in Table 1.

**Table 1 pone.0250111.t001:** Timeline for the schedule of enrollment, assessments, and interventions.

	Enrollment	Month 1		Month 2		Month 3		Follow-up	
		Baseline	Post	Pre	Post	Pre	Post	Month 6	Month 12
Eligibility criteria	x								
Informed consent	x								
Demographic and anthropometric data	x								

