### Economic assessment

Economic assessment will be done from a healthcare and societal perspective. Incremental cost per quality-adjusted life-years (QALYs) of the interventions will be used for cost-effectiveness and cost-utility analysis, considering both healthcare and societal perspectives, measuring direct and indirect costs. The Numerical Rating Scale will be used for cost-effectiveness analysis, and the SF-6D questionnaire will be used for cost-utility analysis. Cost data will be collected by a cost questionnaire that will be sent to the participant via WhatsApp® at 3, 6, and 12 months after baseline. All costs related to menstrual pain will be considered, either direct (costs of the participant to health systems, public and private, and out-of-pocket expenses) and indirect (unpaid productivity loss), which include intervention, healthcare, informal care, and unpaid productivity costs. Intervention costs will be estimated based on the physical therapy board fee schedule (according to the Federal Physical Therapy and Occupational Therapy Council, USD 11.32 per TENS application– 2020 fee which is equivalent to R$ 64.63 rate converted to US dollars using the 04/02/2021 conversation rate [41]). Healthcare costs, including primary and secondary healthcare costs, will be priced using Brazilian standard costs. Both prescribed and over-the-counter medication use will be priced using the prices of the Brazilian pharmaceutical websites and medical services fee schedule.

A Portuguese/Brazil validated version [42] of the Stanford Presenteeism Scale [43] will be used to measure presenteeism from paid work, and the estimated price of productivity losses per sickness absence day for women, according to the average wage in the state of São Paulo per hour.

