**Fig 1 pone.0250111.g001:**
[figure not shown]

All groups will receive an educational booklet containing information on the anatomy of the pelvis, menstrual pain, and recommendations related to dysmenorrhea. The booklet group will not receive additional treatment and will be advised not to receive treatment elsewhere during the first three months of participation in the study. This educational booklet was validated using a modified Delphi method. A group of experts discussed issues related to the practice of physiotherapy in the treatment of PD, while another group read the identified manuscripts and guidelines related to the topic. The experts had six meetings to discuss the findings and propose the booklet. Subsequently, a group of consultants, including physiotherapists who are specialists in women’s health, further analyzed, made additional contributions, and approved the booklet. Several women with DP were also consulted and approved the final version of the booklet.

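### As written, only the booklet arm is advised against outside treatment for three months, so TENS versus booklet at month 3 runs under unequal co-treatment instructions

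*Protocol article*

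**What the plan says.** Eligibility criteria (protocol article) states a rule for the study as a whole: "No concomitant care or interventions will be encouraged or forbidden during the study, but rather registered" in each woman's file.

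Interventions first says what every arm gets, "All groups will receive an educational booklet", and then turns to one arm: "The booklet group will not receive additional treatment and will be advised not to receive treatment elsewhere during the first three months". No section gives the active or placebo TENS arm matching advice.

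Three other statements fix what the advice touches:

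- Assessment of clinical outcomes: "The primary outcome is pain intensity at baseline and three and six months after randomization".
- Abstract: "It is hypothesized that active TENS will be more effective than placebo TENS or the educational booklet".
- Economic assessment: "All costs related to menstrual pain will be considered", with questionnaires at 3, 6 and 12 months.

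Statistical analysis adds that possible confounders, pain medication among them, are recorded and used in the analysis.

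**The concern.** Randomization makes the arms comparable at the start. After that, a fair comparison needs them handled alike except for the treatment under test. Advice to avoid outside care, given to one arm after allocation, is a second difference between TENS and booklet. It operates over the weeks leading up to a primary pain score.

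Two results are at stake. If booklet women follow the advice and give up care that would have helped, their month 3 pain is higher than it would have been, and TENS looks better. If they also spend less on outside care, the booklet arm looks cheaper in the first cost questionnaire, and TENS looks dearer by comparison. One clause can therefore touch both aims of the trial, effectiveness and cost-effectiveness.

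**Working it through.** The plan prints no figure on this point, so the check is mainly a comparison of texts.

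**1. The two instructions side by side**

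| | Eligibility criteria | Interventions |
|---|---|---|
| Applies to | the whole study | the booklet group |
| Outside care | neither promoted nor barred, only recorded | advised against |
| Period | during the study | first three months |

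The Interventions paragraph itself separates what all groups get from what the booklet group gets. As written, the advice is therefore specific to one arm. That it goes to no other arm is an inference from the absence of any such statement for the TENS arms.

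**2. What outside treatment covers.** The natural reading is care from another provider. This includes TENS elsewhere, but also acupuncture, which the Introduction lists among the common non-drug alternatives. Over-the-counter drugs, heat and exercise are mostly self-care and probably fall outside it.

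**3. What lies inside the window.** Month 3 pain (primary) and the first of three cost questionnaires, assuming that questionnaire looks back to baseline. The advice covers 3 of 12 months, or 25% of the cost follow-up. Pain at month 6 (primary) and month 12 (secondary) comes after it ends.

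**4. Direction.** Let b and t be the shares using outside care in the booklet and TENS arms without any advice, p the share of booklet women who forgo it because of the advice, and e its effect on pain. The shift in favour of TENS from unequal outside care is

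(t − b + p) × e.

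If b = t, this is p × e, which is zero or more and favours TENS. If b exceeds t, the advice partly offsets a difference that would have arisen anyway; at b − t = p the shift is zero. The documents give none of b, t, p or e.

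**5. Illustration of size, taking b = t.** The only effect sizes printed are for TENS (Sample size calculation): f = 0.20 for planning and 1.384 from a review. Reading f as a between-group effect across three arms:

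- one arm differs from two equal arms: d = 0.20 × 3/√2 = 0.424 SD
- evenly spread means: d = 0.20 × √6 = 0.490 SD

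| p (assumed) | e = 0.424 | e = 0.490 | e = 1.384 |
|---|---|---|---|
| 0% | 0 | 0 | 0 |
| 5% | 0.021 | 0.024 | 0.069 |
| 10% | 0.042 | 0.049 | 0.138 |
| 20% | 0.085 | 0.098 | 0.277 |

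All entries are in SD units. The last column assumes that 1.384 is in SD units, which the protocol does not say, and uses a value the authors set aside as too optimistic for planning.

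**6. Illustration for costs.** The fee is "USD 11.32 per TENS application". With one session per cycle (an assumption; Table 1 marks one per month), TENS costs 3 × 11.32 = USD 33.96 per woman. If a share p of booklet women forgo three outside sessions at that fee, the booklet arm's mean cost falls by p × 33.96: USD 1.70, 3.40 and 6.79 at 5, 10 and 20%. This ignores any rise in drug or productivity costs from untreated pain, which would work the other way.

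**The case against.** The strongest reply is that this is a sensible guard on a minimal-intervention comparator. Booklet women know that they receive no TENS (Strengths and weaknesses of the study), so without advice they might seek more outside care than the TENS arms. The advice could then narrow a difference rather than create one. This stands: it is the case of b above t in the working, and it is why the direction cannot be called one-sided. It also means that simply deleting the advice trades one problem for another.

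A reader might infer a flat contradiction between the two sections. That goes too far. Advice is not a prohibition, and outside care is still allowed and recorded. The conflict is with the neutrality of the rule, and the inequality between arms remains on either reading.

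Exposure may also be low. Contribution to professionals and patients says that women do not often seek help for this pain, so few may have care to forgo and p may lie near the bottom of its range. This stands too.

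Two replies do not remove the point. Recording co-treatment and using it in the analysis makes an imbalance visible, but co-treatment after randomization is itself changed by the advice, so adjusting for it does not reliably undo the effect. And condensation in an article may explain silence about the TENS arms, but not two printed instructions that do not fit together. The full protocol or participant scripts might show the same advice for all arms; if so, a wording correction is enough.

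**Conclusion.** The point holds in a limited form. The protocol article states a neutral co-treatment rule and then gives the booklet arm, and as written no other arm, advice that departs from it up to the month 3 primary score. The TENS-versus-booklet comparison of month 3 pain, and the costs in the first questionnaire, therefore run under unequal instructions.

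A reader might infer that month 3 pain is biased in favour of TENS by a known amount. The documents do not support that. The direction is likely but rests on equal outside care without the advice. The size rests on an assumed p and on TENS effects borrowed for other care. With the planning effect, the illustration gives 0 to 0.10 SD, against a design effect of 0.42 to 0.49 SD, and it may be close to zero.

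Nor does the point reach the whole trial. Active versus placebo TENS is untouched, and later pain scores are not directly under the advice. TENS versus booklet is already open to the booklet women, which the authors acknowledge and cannot avoid. This further difference they can avoid at little cost, which is why the change is worth making.

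**What to change.** Give all three arms the same co-treatment instruction in the same words, and make the two sections agree. For example, advise every woman against TENS or physiotherapy for period pain from another provider until her month 3 score, with usual pain drugs allowed and recorded. Name this as the one exception to the neutral rule in Eligibility criteria. Report co-treatment by arm at months 3 and 6.

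This keeps the guard against outside TENS and removes the inequality. It costs one sentence in each of Eligibility criteria and Interventions and one participant script; endpoint, visits and sample size stay as they are. The downside is a slight restriction of usual care in the TENS arms, which may lower their recorded healthcare costs for 3 of the 12 months of the economic evaluation.

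Deleting the booklet-only advice would also equalise the arms, but it gives up the guard and may let outside treatment dilute the contrast.

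If women were already enrolled under the booklet-only advice, state it as a limitation of the TENS-versus-booklet comparison.

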### Assessment of clinical outcomes

Participants who agree to participate will be assessed by a blinded assessor who will check for eligibility criteria. Subsequently, the blinded assessor will collect participants’ demographic and anthropometric data and information regarding menstrual pain medication use. Next, all eligible participants will be randomized and allocated into three groups: active TENS (aTENS), placebo TENS (pTENS), and minimum intervention group (booklet). The same blinded assessor will evaluate primary and secondary outcomes.

The primary outcome is pain intensity at baseline and three and six months after randomization. The secondary outcomes are pain intensity (only at 12 months after randomization, for the cost-utility analysis), health-related quality of life at 6 and 12 months after randomization, and pain intensity at each session before and after treatment for three months for the TENS groups. All assessment sessions are described in Table 1.

**Table 1 pone.0250111.t001:** Timeline for the schedule of enrollment, assessments, and interventions.

	Enrollment	Month 1		Month 2		Month 3		Follow-up	
		Baseline	Post	Pre	Post	Pre	Post	Month 6	Month 12
Eligibility criteria	x								
Informed consent	x								
Demographic and anthropometric data	x								

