**Interventions**									
Active TENS			x	x		x			
Placebo TENS			x	x		x			
Educational Booklet			x						

To evaluate pain intensity, an 11-point NRS will be used, where 0 (zero) represents no pain and 10 (ten) represents the greatest imaginable pain. Participants will be instructed to rank their pain according to the appropriate point of the scale [35].

Health-related quality of life will be evaluated for Short-Form 6 dimensions (SF-6D) [36, 37], a multi-attribute utility instrument translated and validated to Portuguese/Brazil [38]. It measures health on six dimensions: physical functioning, role limitations, social functioning, pain, mental health, and vitality. The SF-6D unique score varies from 0 (worst health state) to 1 (best health state) and represents the strength of an individual’s preference for a given health state.

Conventionally, it has been recommended to use SF-6D together with the 36-Item Short Form Health Survey questionnaire (SF-36) [37]. The SF-36 [39, 40] assesses health-related quality of life in eight domains: physical functioning, role physical, bodily pain, general health, vitality, social functioning, role-emotional, and mental health. The SF-36 scores represent a health status and range from 0 (worst health status) to 100 (best health status) for each domain.

The baseline assessment will be performed face-to-face for all participants. Participants allocated to the TENS groups will respond to pain intensity face-to-face, before and after each treatment session, during three consecutive menstrual cycles. During this period, participants allocated to the educational booklet will be assessed using text messages and/or video calls with WhatsApp®. In the three-month assessment, the participants of all groups will also be asked about their satisfaction with the treatment. The 6- and 12-month assessments will be conducted using WhatsApp®. The timeline for the schedule for enrollment, assessment, and interventions is presented in Table 1.

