### Strengths and weaknesses of the study

The strengths of the present study are that this is the first prospective study that aimed to assess the cost-effectiveness of TENS for PD pain. This is a randomized controlled clinical trial in which researchers, participants, and physical therapists are blinded to participants’ allocation and to the aim of the present study. The sample size was appropriately calculated to provide enough power to detect differences in the primary outcome. The statistical plan analysis includes the intention-to-treat analysis and intends to assess all women who discontinue intervention. One limitation of the present study is that even though participants allocated to the TENS groups (both active and placebo) will be blinded to their allocation, it is not possible to blind participants in the Booklet group.

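### The trial-wide claim of one blinded assessor conflicts with the arm-dependent collection of pain scores for TENS versus booklet, and at month 3 collection mode is confounded with arm

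*Protocol article*

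**What the plan says.** Three places in the protocol article claim blinding beyond that of the TENS participants.

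- Abstract: "This is a protocol for an assessor-blinded randomized controlled trial".
- Assessment of clinical outcomes: "The same blinded assessor will evaluate primary and secondary outcomes".
- Strengths and weaknesses of the study: the trial is presented as one "in which researchers, participants, and physical therapists are blinded to" allocation. The only limitation admitted is that women in the booklet group cannot be blinded; the assessor is not mentioned.

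Assessment of clinical outcomes also defines the main endpoint: "The primary outcome is pain intensity at baseline and three and six months after randomization". Its list of secondary outcomes includes session-level pain for the TENS groups only. Table 1 puts the primary pain score at Baseline, Month 3 Post and Month 6.

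The text after Table 1 gives the collection routes.

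- Baseline: "The baseline assessment will be performed face-to-face for all participants".
- Treatment cycles, TENS arms: "Participants allocated to the TENS groups will respond to pain intensity face-to-face, before and after each treatment session, during three consecutive menstrual cycles".
- Treatment cycles, booklet arm: "participants allocated to the educational booklet will be assessed using text messages and/or video calls with WhatsApp".
- Later follow-up: "The 6- and 12-month assessments will be conducted using WhatsApp".

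**The concern.** A person who sees some women before and after stimulation sessions and contacts others only by message or video knows who is in the booklet arm. If that person is the single outcome assessor, assessor blinding does not exist for TENS versus booklet, although the Abstract claims it for the trial as a whole and the Discussion lists blinding of researchers as a strength.

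A second problem does not depend on who collects the scores. At the month-3 primary assessment the TENS arms are rated in person and the booklet arm remotely, so any effect of mode on reported pain falls into the TENS-booklet difference.

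Active TENS versus booklet is one of the two comparisons in the Abstract's hypothesis, so this is not a side contrast. Readers would take an assessor-blinded label at face value for it.

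**Working it through.** The plan gives no figure to reproduce. The check sets the collection route beside the blinding claim at each timepoint.

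| Timepoint | Primary pain score (Table 1) | TENS arms | Booklet arm | Does the route reveal the booklet arm? |
|---|---|---|---|---|
| Baseline | yes | in person | in person | no |
| Months 1 and 2 | no | in person, around sessions | WhatsApp text or video | yes, to whoever collects |
| Month 3 Post | yes | in person, around sessions | WhatsApp text or video | yes, to whoever collects |
| Month 6 | yes | WhatsApp | WhatsApp | no, but earlier knowledge may carry over |
| Month 12 | no | WhatsApp | WhatsApp | no, but earlier knowledge may carry over |

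**Step 1: who collects.** The text after Table 1 names nobody as recording the session scores or sending the messages. There are two cases.

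- *The assessor collects them.* The session outcome and the route separate TENS from booklet completely. What the assessor learns can carry to months 6 and 12, because the same assessor is to evaluate all outcomes.
- *Someone else collects them.* The assessor is not unblinded by this route. But session pain is a listed secondary outcome and Month 3 Post is a primary one, so the statement that one assessor evaluates all of them is then wrong.

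The sections conflict in both cases.

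**Step 2: mode at month 3.** Let d be the true TENS-minus-booklet difference in pain at month 3, and m the shift in reported pain from answering remotely instead of in person. The observed difference is d − m, because only the booklet arm carries m. The baseline was in person for everyone, so adjusting for it does not remove m. Blinding the statistician, as the Statistical analysis section provides, does not remove it either. The documents give no value for m.

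**Step 3: extent.**

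- 174 / 3 = 58 women are in the booklet arm.
- Three arms give three pairwise contrasts. Two involve the booklet: active TENS versus booklet, and placebo TENS versus booklet.
- Of the two post-baseline primary timepoints, one (month 3) has a route that differs by arm.
- Active and placebo TENS share the same route throughout, so m cancels and the route tells the assessor nothing about which device was used.

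**The case against.** The strongest reply has three parts.

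1. **The documents do not show that the assessor is unblinded.** They do not say who attends sessions or handles the messages, and an article may leave staffing to the full protocol. This stands as far as it goes. A reader might infer that the same assessor certainly rates TENS women at sessions and then makes every later contact; the text supports that only through the general sentence on the single assessor. The conflict remains, because that sentence cannot be accurate alongside the other reading.

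2. **The added harm is limited.** Pain is self-rated, booklet women may answer by text with little prompting, and their knowledge of their own arm is already admitted. This also stands. An unblinded questioner adds to a disclosed bias only through eliciting and recording the answer. But that addition is not disclosed, and the difference in mode at month 3 is separate from it.

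3. **Most timepoints share one route.** Correct for baseline and for months 6 and 12. At month 6 any loss of blinding depends on the assessor having learned the arm earlier and remembering it. The text also mentions a three-month assessment of all groups without giving its route. The month-3 point therefore rests on Table 1, which places the primary score at Month 3 Post, within the treatment cycles.

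**Conclusion.** The claim of assessor blinding needs correction for TENS versus booklet. Either the assessor learns who is in the booklet arm, or the single-assessor statement is inaccurate; and at month 3 collection mode is confounded with arm. This affects two of three pairwise contrasts, most clearly at one of the two post-baseline primary timepoints. It assumes that the Month 3 Post score follows the routes given for the treatment cycles.

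Several stronger readings are not supported:

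- Active versus placebo TENS is not compromised by the route.
- No bias in pain-scale points can be stated, because the documents contain nothing from which to derive one.
- TENS versus booklet cannot be called the cost-effectiveness contrast. The Economic assessment and Statistical analysis sections choose no single comparator.
- The finding does not require active versus placebo to become the only efficacy contrast. That would change the stated hypothesis, which covers both comparators.

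**What to change.** 1. Collect the primary pain score at months 3 and 6, the 12-month pain score and the follow-up SF-36 on one identical self-completed form, sent to all arms through the existing WhatsApp channel. Keep it separate from the session ratings, and align Table 1's Month 3 Post entry with it.
2. Have session scores recorded by someone other than the outcome assessor, for example the therapist already present, and say so in Assessment of clinical outcomes.
3. Unless these changes are made, restrict the assessor-blinding claim in the Abstract, in Assessment of clinical outcomes and in Strengths and weaknesses to active versus placebo TENS, and add the unblinded TENS-booklet assessment to the limitations.

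The cost is small: a form, a revised table entry and some wording. If the collection is left as it is, the blinding claim becomes slightly less favourable. If the form is adopted, mode changes between the in-person baseline and follow-up, but equally in all arms, so a common mode effect cancels from between-group differences. The form does not cure booklet women's knowledge of their own arm; that limitation is already stated and should stay.
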